#### Ethical approval and trial registration

The study has the approval of the Ethical Committee of the Hospital Universitari Sant Joan de Reus (ref: 14–04–24/4proj2), and the trial was registered with clinicaltrials.gov (NCT02157402).

The protocol is in accordance with the Helsinki Declaration and the good clinical practice guidelines of the International Conference of Harmonization (ICH GCP). This randomised trial was conducted according to the extended cluster CONSORT 2010 guidelines.

#### Additional information

This study followed the SPIRIT [37] and TIDieR protocol description recommendations [38] as presented in Additional file 1 and Additional file 2. The participation, schedule of enrolment, interventions and assessment are presented in Table 4. Finally, a cluster CONSORT checklist and flow diagram were used to summarise the description of study when the study and analysis were completed [39].

**Table 4 Tab4:** Spanish EYTO participation, schedule of enrolment, interventions and assessment

	Study period							
	Enrolment	Allocation	Post-allocation					
	Phase 1				Phase 2			Phase 3
Timepoint	-t_1_	a0	t_1_	t_2_	t_3_	t_4_	t_5_	t_6_
	May 2014_(after CEIC approval)_	May 2014	May 2014	May 2014	May 2014	September 2014	September 2014	October 2014
	High-Schools of low income in Reus are included in this phase.	4 high-school are randomly chosen, 2 in the intervention and 2 in the control group	Control High-school meeting, Separate Intervention high-school meeting and 5 ACC selection	Social marketing, health promotion and communication training for 5 ACCs	Each participant answered the HBSC Survey.	Implementation of challenges by the 5 ACCs with help of stakeholders for their peers.	Preparation of the ACC presentation of the first academic Spanish intervention at the EYTO meeting in London.	Meeting of 5 ACCs from the 4 EYTO participating countries in London to pool designed activities and exchange ideas. Successful intervention activities can be re-implemented.
	Randomisation is performed.			Design of the intervention. Information and informed consent signed	Implementation of interventions by the 5 ACCs for their peers in high-school for 12 weeks.			
Enrolment:	360–400 adolescents from low-income neighbourhoods.							
Eligibility screen	X		X					
Informed consent								
[List other procedures]								
Allocation	180–200 from intervention group and 180–200 from control group							
Intervention			Training of 5 ACCs to design activities		HBSC Survey Implementation of activities during 12-week period	Implementation of social event challenges in the community and local markets for their peers		Evaluate the activities performed during 12-week period (1^st^ academic year)
Control			This group did not receive any interventions		HBSC Survey			
Assessments: List baseline variables	X	X	X				X	X
List primary and secondary outcome variables for 200 participants in the intervention and 200 participants in the control group			Fruit and vegetable consumption, breakfast consumption, physical activity practice and sedentary behaviours.					
Study period								
	Post-allocation					Close-out September 2015		
	Phase 4			Phase 5				
Timepoint	t_7_	t_8_	t_9_	t_10_	t_11_	t_12_		
	November 2014	February 2015	Mar 2015	Sept 2015	Sept 2015	Sept 2015		
	Activities re-implemented by 5 ACCs for their peers in the intervention group high-schools during a 12-week period (2^nd^ academic year)	Challenges designed by the 5 ACCs for their peers with stakeholder help	Preparation of the presentation on the Spanish intervention for the EYTO meeting in Spain	Meeting of 5 ACCs from the 4 EYTO participating countries in Reus, Spain.	Report of intervention challenges to the 4 EYTO countries and web presentation and analysis of data.	EYTO Final report including intervention challenges and Results of lifestyle outcomes		
Interventions:								
Intervention	Implementation of activities during a 12-week period (2^nd^ academic year)	HBSC Survey Intervention implementation						
Control		HBSC Survey						
Assessments:			X	X				
List primary and secondary outcome variables								
for 200 participants in the intervention and								
200 participants in the control group		February 2015, at the end of intervention		End of the participation of the 5 ACCs	Fruit and vegetable consumption.			
					Physical activity Practice. Sedentary behaviours.			

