### Spanish study design

The “Som la Pera” intervention is a school cluster randomised controlled trial. The participating Spanish city was Reus (Catalonia). Local authorities have already identified public high-schools that they agree serve low-income neighbourhoods that are considered disadvantaged areas. From the 9 public high-schools identified in these neighbourhoods, 4 high-schools were randomly selected. The randomisation code was computer generated. The high-schools were assigned to the control or intervention arm at a ratio of 1:1 via an interactive electronic response system hosted by the Nutrition and Health Technology Centre (CTNS) in Reus, Spain. The unit responsible for the randomisation took no further part in the study. Because the researchers know the names of the four high-schools, allocation concealment was not performed. The project consists of five main phases, as shown in Fig. 1. The first phase included the randomisation and allocation of the high-schools in the disadvantaged area into the two intervention and two control high-schools. High-school teachers from the randomised intervention group selected the five adolescents according to their knowledge of the students by considering leadership characteristics and English level (because the students will participate in EYTO European meetings), 2 adolescents from one high-school and 3 from the other high-school. These 5 adolescents will be referred to in this protocol as the Adolescent Challenge Creators (ACCs). The study characteristics are summarised in Table 1.

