The professional experts who participate in “Som la Pera” intervention are:Physicians: physicians specialist on health education and promotion led the implementation of the study from the recruitment process to the end of the experimental protocol by meetings with stakeholders like high-schools’ director or local policy-makers and health and educators administrators. They were in charge of designing, performing and revising the evaluation process throughout the study.Nutritionists: nutritionists with expertise on health education and health promotion led the high-school recruitment process by meetings with parents and adolescents explaining the project, recollected the informed consent of parents and adolescent to participate in the study and, coordinated the logistical issues of the study. They contributed to support the evaluation of primary and secondary outcomes through the validated questionnaire in high-schools computer classrooms to solve adolescents’ questions of lifestyles and behaviour evaluation questionnaire. The nutritionists were responsible for the dietary and healthy lifestyle training of the 5 ACCs.Managers: The managers coordinated the Spanish intervention among the participating countries. They supervised all of the scientific work, from the intervention trial design to the scientific data interpretation.Publicists and Journalists: publicists and journalists experts on health communication were responsible for the communication training of the 5 ACCs. Even though the 5 ACCs were in charge of the communication and dissemination campaign (lifestyles messages and intervention challenges), publicists and journalists are in charge to disseminate the general information of this intervention and European project to general population through local, national and international newspapers and television media.

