### Evaluation process

#### Primary and secondary outcomes

The expected primary outcomes of the Spanish intervention were as follows: increases in the consumption of fruits and vegetables and physical activity practice, along with reductions in TV/computer/game console use. The secondary outcomes were as follows: increased breakfast consumption, engagement with local recreation and reduced obesity prevalence. The outcomes of the Spanish intervention were measured by the Health Behaviour in School-aged Children Study (HBSC) Survey 2009–2010 [35] to evaluate the adolescents’ lifestyles at baseline and at the end of the intervention as presented in Table 3. The HBSC study is a validated cross-sectional survey of school students that collects data every four years on 11-, 13- and 15-year-old adolescents [36]. The baseline measurements from the intervention and control groups were performed in the second phase, and the end-of-study measurements were performed in the fourth phase (Fig. 1). Analyses and evaluations of each country’s intervention and global project will be performed in phase 5 (Fig. 1) so that the project can be concluded.

**Table 3 Tab3:** Outcomes measurements in the Health Behaviour in School-aged Children Study (HBSC) Survey

Health Behaviour in School-aged Children Study Items	Outcome measured	Question	Possible answers
Eating habits	Nutritional behaviour. Fruit, vegetable and water consumption.	How many times a week do you usually eat or drink (fruits, vegetables, sweets, coke or other soft drinks that contain sugar)…?	Never, less than once a week, once a week, 2–4 days a week, 5–6 days a week, once a day, every day, every day more than once every day.
(primary outcomes)	Breakfast quantity and quality	How often do you usually have breakfast (more than a glass of milk or fruit juice)?	*Weekdays* (I never have breakfast, one day, two days, three days, four days, five days).
			*Weekends* (I never have breakfast during the weekend, I usually have breakfast on only one day of the weekend (Saturday OR Sunday), I usually have breakfast on both days (Saturday AND Sunday)).
Physical activity	Physical activity practice	Over the past 7 days, on how many days were you physically active for a total of at least 60 min per day?	0 days, 1 day, 2 days, 3 days, 4 days, 5 days, 6 days, 7 days.
(primary outcomes)			

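### Pupil consent and the baseline survey appear to follow an open allocation of schools, so membership of the analysis set could depend on arm

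*Protocol article*

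**What the plan says.** All references are to the protocol article.

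- **Allocation.** Table 4 (Additional information) has, at a0 in May 2014, "4 high-school are randomly chosen, 2 in the intervention and 2 in the control group". The section on the Spanish study design agrees: "The first phase included the randomisation and allocation of the high-schools in the disadvantaged area into the two intervention and two control high-schools".
- **First contact after allocation.** At t1, under the post-allocation heading: "Control High-school meeting, Separate Intervention high-school meeting and 5 ACC selection".
- **Consent.** At t2: "Design of the intervention. Information and informed consent signed". This is the only dated consent entry in the table; the row reserved for informed consent is blank.
- **Baseline.** At t3: "Each participant answered the HBSC Survey". The section on primary and secondary outcomes agrees: "The baseline measurements from the intervention and control groups were performed in the second phase".
- **Concealment.** Spanish study design: "Because the researchers know the names of the four high-schools, allocation concealment was not performed".
- **Who recruits.** The participants section says that the nutritionists met parents and adolescents to explain the project and "recollected the informed consent of parents and adolescent to participate in the study". The same professionals train the ACCs.
- **Who is analysed.** Inclusion requires attendance at one of the schools already randomised and signed parental consent. The statistical analysis plan section defines the intention-to-treat set by the presence of baseline efficacy data.

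**The concern.** Randomising schools balances, in expectation, the pupils who attend them. It does not balance the pupils who agree to take part if agreement is sought once the arm is known. Here one arm is offered a two-year lifestyle programme and the other only questionnaires, and the outcomes are self-reported lifestyle behaviours. It is plausible that keener families would join more readily where there is a programme. Because the analysis set requires consent and a completed baseline survey, both apparently obtained after allocation, an intention-to-treat analysis of that set would not undo such selection.

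The rationale given for non-concealment also fails on its own terms. Knowing the names of four schools is not knowing which arm each will get. The draw can be made, or its result withheld, until pupils are enrolled.

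**Working it through.** **1. Order of events.** In Table 4 the sequence is allocation (a0), separate meetings by arm and ACC selection (t1), information and consent (t2), baseline survey (t3). The text supports the two ends: randomisation is in phase 1 and baseline in phase 2. The inclusion criteria, which refer to schools already randomised, support consent after allocation. Nothing in the article places pupil consent before allocation or describes a safeguard.

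**2. The plan's own figure.** It states 121 per group, 90 % power, two-sided 5 % and a difference of 0.5 portion, but no SD. Solving backwards with the normal approximation:

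SD = 0.5 / [(1.960 + 1.282) × √(2/121)] ≈ 1.20.

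An alternative reading is SD 1.0, which needs 85 evaluable pupils, and 85 / 0.70 rounds up to 122. Neither reading bears on the point. SD 1.2 is used below as an assumption.

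**3. Assumed illustration, end-of-study comparison without baseline.** Let a share q of the intervention sample be joiners who eat D portions more than the pupils they replace. The shift in the arm mean is b = q × D. For q = 0.10 and D = 1, b = 0.10 portion, and 0.10 / 0.5 = 20 % of the target. With SE = 1.2 × √(2/121) = 0.154, and no true effect, the chance of a significant result is Φ(−1.96 + b/SE) + Φ(−1.96 − b/SE):

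| q | D = 0.5 | D = 1.0 | D = 1.5 |
|---|---|---|---|
| 5 % | 0.025 (5.3 %) | 0.05 (6.2 %) | 0.075 (7.7 %) |
| 10 % | 0.05 (6.2 %) | 0.10 (9.9 %) | 0.15 (16.3 %) |
| 20 % | 0.10 (9.9 %) | 0.20 (25.4 %) | 0.30 (49.4 %) |

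Cells give the bias in portions and, in brackets, the rejection rate. The values of q and D are not in the article, and clustering is ignored.

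**4. The same joiners when change is analysed.** If they eat D more at both time points, the arms differ by b at baseline and by b at follow-up. The difference in change is b − b = 0. Bias remains only if joiners would change differently without the programme. If their extra change is d, the bias is q × d. To reach 0.10 portion with q = 0.10, d must be 0.10 / 0.10 = 1 portion, twice the target effect; with q = 0.20, d must be 0.10 / 0.20 = 0.5 portion.

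**The case against.** The strongest reply has four parts.

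- **The table may not show what it seems to.** The t2 column also covers ACC training and design, so its consent entry could be the ACCs' alone. The t1 meetings may have been with school staff. An eligibility mark and the planned 360–400 adolescents stand in the first column, before a0. This is why the order is put here as apparent. It remains the likelier reading: t2 is the only dated consent entry, a second eligibility mark stands at t1, and the inclusion criteria presuppose randomised schools.
- **Knowledge of the arm is inferred.** A reader might conclude that families knew the arm when they decided, or that consent did differ between arms. The article supports neither: it does not say what families were told and gives no consent figures. Separate meetings and the absence of concealment make such knowledge plausible, no more.
- **The planned analysis deals with much of it.** The statistical analysis plan section uses generalised linear mixed models for changes from baseline. A persistent level difference then largely cancels, as step 4 shows. This part stands. It does not cover differences in readiness to change.
- **Imbalance would be visible.** Both arms are surveyed at baseline, so it would go too far to say that selection could not be told from an effect. Differences in the measured outcomes would show. Unmeasured motivation would not, and two schools per arm give little basis for separating it from an effect.

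**Conclusion.** The point holds as a risk built into the sequence, not as a demonstrated bias. On the likelier reading of Table 4, consent and baseline come after an open allocation, and together they decide who is analysed. The stated reason for not concealing does not justify that order.

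The size cannot be fixed from the article. The 0.1 portion, or 20 % of the target, rests on assumed values and applies only to an end-of-study comparison that ignores baseline. It should not be read as the bias of the planned analysis of change, where only a different rate of change among joiners would matter. That part has no figure in the article, and baseline data cannot fully reveal it.

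**What to change.** **In the plan.** Hold one identical information meeting in all four schools, obtain consent and the HBSC baseline, then draw or disclose the allocation, and only then select the ACCs. Table 4 places all these steps in May 2014, so the change is one of order within the month.

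**As the article reports these steps as done:**

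1. State when pupil consent was sought relative to allocation, and what families and recruiters knew of the arm.
2. Report pupils approached and consenting by school and arm, with baseline characteristics. The cluster CONSORT flow diagram already promised can carry the counts.
3. Include the baseline outcome value in the mixed model explicitly, and say in what form. As a repeated measure with a group-by-time term and separate arm means at baseline, a persistent gap cancels. As a covariate with slope β, a share (1 − β) of the gap remains.
4. Qualify the conclusion for possible selection after open allocation.

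The cost is a sentence on timing, one table, one model term and a sentence of limitation.

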## Discussion

This paper describes an intervention aimed at improving lifestyles, such as nutritional habits and physical activity practice, for obesity prevention in socioeconomically disadvantaged and vulnerable adolescents.

Based on the worldwide current high rates of childhood and adolescent obesity [9], the fight against adolescent OB is a significant public health objective. This focus indicates the necessity of new methodologies to achieve adolescent behaviour changes [40]. Social marketing nutrition interventions were strongly and equally effective at influencing nutrition behaviour, knowledge and psychosocial variables, suggesting that social marketing interventions can produce changes across different behaviours [41]. There is growing evidence that interventions using social marketing approaches can contribute to encouraging healthier lifestyles and, as a result, can prevent obesity [21].

An important problem in the field of social marketing research is that there are some interventions that use social marketing principles in their study design without being aware of that fact [42]. Additionally, few interventions that use the principles consciously publish the obtained results. One such intervention is Change4Life, a national social marketing program, implemented in the United Kingdom to reduce obesity [35]. This intervention achieved increased awareness of the anti-obesity campaign but had little impact on attitudes and behaviours. The peer-led model is effective when it is applied in school-based studies and generates more positive results in health behaviour than adult-led instruction [33]. Also, key principles to create new approaches that fight obesity are set to guide the development of strategies to address unhealthy diets and physical inactivity, and should include: best available scientific evidence, comprehensiveness, multisectoral and multidisciplinary approaches, a life course perspective, addressing poverty, gender and culture sensitivities, and the accountability of all stakeholders to achieve success [43].

Despite their considerable complexity, it is crucial to assess the outcomes achieved in interventions that employ social marketing principles. In this way, the public health sector of the government will be able to distribute its efforts to address adolescent obesity more efficiently [40].

## Abbreviations

EYTO: European Youth Tackling Obesity
ACCs: Adolescent Challenge Creators
HBSC: Health Behaviour in School-aged Children Study
SMBC: Social Marketing National Benchmark Criteria
